### Sample Size Estimation

This clinical study is a superiority, randomized parallel controlled trial. GnRH-a+hCG (dual trigger) in group A and hCG-only trigger in group B. MII oocytes rate will be the primary outcome measurement. According to previous data of our centre, the estimated rate of MII oocytes in group B was **40%**, and **70%** in group A after using GnRH-a (40h before OPU) + hCG (34h before OPU) dual trigger, with **standard deviations of 40%** for each group. Suppose that α=0.05 (two-sided) and β=0.10 (90% power), the sample size is calculated to be 40 individuals for each group by PASS 15.0 (NCSS, LLC. Kaysville, Utah, USA.). Assuming a dropout rate of 10%, the sample size 45 individuals for each group will be required. Ultimately, a total of 90 individuals will be recruited for this study.

### Data Statistical Analysis

All randomized individuals will be included in the analysis of the primary trial end point (intention-to-treat analysis). For analyses of other outcome variables, only subjects randomized to the study protocol will be included (per-protocol analysis). SPSS version 26.0 and R statistical package version 4.0.0 will be used to analyse all the data. The continuous data will be normalized using the two independent samples t-test and presented as mean ± standard deviation (Mean ± SD). If the distribution is not normal, use nonparametric tests, which are expressed as the median (interquartile range) [M (IQR)]. Categorical data will be presented as frequency (percentage) [n (%)] using chi square test and Fisher’s exact test for expected frequencies less than five. P < 0.05 indicates that the difference is statistically significant.

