Trigger methods are related to the number of oocytes retrieved, mature oocytes, 2PN fertilisation rate, number of top-quality embryos, embryo implantation rate, clinical pregnancy rate, miscarriage rate, ongoing pregnancy rate, live birth rate, etc. The acquisition of mature oocytes is required prior to initiating IVF-ET. Obtaining higher-quality embryos is critical for IVF-ET success. The ultimate aim of IVF-ET is to maintain pregnancy and deliver a live baby. Therefore, a comprehensive evaluation of the patient situation and individualized formulation of the appropriate trigger method and trigger dosage are necessary. Previous studies have been compromised by sample size, data statistics, or technique, and debate has persisted about the study’s conclusions. The study is a prospective randomized superiority parallel controlled trial, we aimed to investigate whether co-administration of GnRH-a and standard dose hCG trigger could improve oocyte maturation, embryo quality and pregnancy outcomes in normal responders with poor oocyte maturation rates by prolonging the time between trigger and oocyte retrieval.

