#### Dropout Criteria

Participants who do not fulfil the inclusion criteria, do not adhere to standard treatment procedures, or refuse to sign an informed consent form as a result of a departure from the clinical trial protocol should be eliminated after enrolment. Participants that fulfilled the inclusion criteria but were dislodged from the clinical trial for various reasons, including two instances when the subject withdrew on their own and when the investigator noticed the subject had withdrawn.

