### Study Case Discontinuation

Subjects in the study who experience serious adverse reactions, special physiological reactions, other unexpected events, or who are not suitable to continue participating in the trial will be terminated from the trial. Urgent measures will be taken during the study if the subject has a serious complication or if the condition worsens.

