### Reproductive Outcomes

The primary outcome is MII oocytes rate (percentage of the number of mature oocytes to the number of oocytes retrieved).

The secondary outcomes are number of oocytes retrieved, fertilization rate (the proportion of oocytes that become fertilized), top quality embryos (TQE) rate (percentage of the number of TQE to total embryos obtained), blastula formation rate, embryo implantation rate (percentage of the number of gestational sac to the total transferred embryos), clinical pregnancy rate (percentage of participants with clinical pregnancy), miscarriage rate (percentage of participants with loss of a diagnosed clinical pregnancy before 12 weeks gestation), live birth rate (the proportion of a delivery of one or more living infants), cumulative pregnancy/live birth rates (percentage of participants with clinical pregnancy/live birth after one year of follow-up), severe OHSS rate (percentage of participants with OHSS). TQE was defined as seven or more blastomeres on day three, evenly sized blastomeres, and less than 20% fragmentation, whereas low quality embryos were characterized as anything else. On transvaginal ultrasonography, clinical pregnancy was defined as the appearance of a gestational sac and foetal heartbeat.

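### All outcomes other than the MII rate are labelled per-protocol, so pregnancy, live birth and severe OHSS have no stated comparison as randomised

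*Protocol article*

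**What the plan says.** The Data Statistical Analysis section defines two analysis sets in consecutive sentences. The first reads: "All randomized individuals will be included in the analysis of the primary trial end point (intention-to-treat analysis". The second reads: "For analyses of other outcome variables, only subjects randomized to the study protocol will be included (per-protocol analysis".

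Reproductive Outcomes shows what falls under each. The first covers one outcome: "The primary outcome is MII oocytes rate (percentage of the number of mature oocytes to the number of oocytes retrieved". All the others are secondary and so fall under the second sentence: oocytes retrieved, fertilisation, top-quality embryos, blastula formation, implantation, clinical pregnancy, miscarriage, cumulative pregnancy and live birth, as well as "live birth rate (the proportion of a delivery of one or more living infants" and "severe OHSS rate (percentage of participants with OHSS".

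Two sections describe removal of women. Dropout Criteria lists, among those to be eliminated after enrolment, participants who "do not adhere to standard treatment procedures, or refuse to sign an informed consent form as a result of a departure from the clinical trial". Study Case Discontinuation ends trial participation for "Subjects in the study who experience serious adverse reactions, special physiological reactions, other unexpected events", and for women judged unsuitable to continue. Randomization and Blinding states that patients and doctors are not blinded, while outcome assessors are.

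**The concern.** Membership of a per-protocol set is decided by what happens after allocation. Adherence, withdrawal and adverse reactions can all depend on the trigger a woman received and on how her cycle is going, and she and her doctor both know the arm. The arms also differ in what adherence demands: one injection at 36 hours before retrieval, against two at 40 and 34 hours. A difference between per-protocol subsets may therefore reflect who was removed and not what the trigger did. In a superiority trial this set is not the conservative choice.

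This bears on a stated aim. The Introduction asks whether the dual trigger "could improve oocyte maturation, embryo quality and pregnancy outcomes in normal responders with poor oocyte maturation rates". Under the text as written, only the oocyte maturation part of that aim has an analysis protected by randomisation. The named safety outcome, severe OHSS, has none, and no separate safety set is stated.

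**Working it through.** **1. The plan's own figures (Sample Size Estimation).** Inputs: MII rate 40% against 70%, so δ = 0.30; SD 0.40; two-sided α = 0.05; power 90%; dropout 10%.

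- Normal approximation: n = 2(1.960 + 1.282)² × 0.40² / 0.30² ≈ 37.4, so 38 per arm. The noncentral t gives 39 (power 0.905), and 40 gives 0.912. The stated 40 is reproduced within 2.
- Dropout: 40 / (1 − 0.10) = 44.4, so 45 per arm and 90 in total, as stated.

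The sample size rests on the primary outcome, so a change of analysis set for the secondary outcomes leaves it alone. Analysed as randomised, a secondary comparison would use 45 against 45. If per-protocol exclusions happened to match the 10% allowance, it would use about 40 against 40.

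**2. The wording of the second sentence.** The inclusion rule, read literally, admits every randomised woman. The label, the word only, and the contrast with the intention-to-treat sentence before it all point to a narrower set. If all randomised women are meant, the label is wrong. If the label is meant, the rule is wrong. Per-protocol is the likelier reading.

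**3. How large could the distortion be?** The documents give no expected live birth or OHSS rate and no exclusions by arm, so this is an illustration. Assumptions, none of them from the documents:

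- the true live birth rate is the same in both arms, at 20%, 30% or 40% of 45 (9, 13.5 or 18 expected births);
- nine women are excluded (10% of 90, borrowing the dropout allowance as a scale);
- none of the excluded women has a live birth.

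False difference = births/(45 − a) − births/(45 − b), where a and b are the exclusions in each arm.

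| Split a:b | 20% | 30% | 40% |
|---|---|---|---|
| 5:4 | 9/40 − 9/41 = 0.5 points | 13.5/40 − 13.5/41 = 0.8 | 18/40 − 18/41 = 1.1 |
| 7:2 | 9/38 − 9/43 = 2.8 | 13.5/38 − 13.5/43 = 4.1 | 18/38 − 18/43 = 5.5 |
| 9:0 | 9/36 − 9/45 = 5.0 | 13.5/36 − 13.5/45 = 7.5 | 18/36 − 18/45 = 10.0 |

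With all 90 women analysed as allocated, the difference is 0 in every cell. What matters most is the imbalance of exclusions between arms: with an equal split the bias vanishes under these assumptions.

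**The case against.** The strongest reply has five parts.

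- *The primary outcome is protected.* It is analysed by intention-to-treat. The secondary outcomes carry no power claim in a 90-woman trial, and the Discussion presents the results as support for a further trial. This stands and limits the weight of the point. It does not remove it, because pregnancy outcomes are part of the stated aim.
- *There is little time for departures.* Randomisation is on the trigger day and retrieval follows within about 40 hours. This stands for oocyte number. It is weaker for pregnancy, live birth and one-year cumulative outcomes, where removal can occur at or after retrieval and transfer.
- *OHSS cases are not dropped.* A reader might infer that women with severe OHSS are removed from the very set in which OHSS is counted. The text does not say so. Study Case Discontinuation does not name OHSS and does not say that women who are terminated leave an analysis set. The adverse events section follows serious events to resolution, and the Ovarian Stimulation Protocol handles high OHSS risk on the trigger day within the protocol. What remains is a possibility: the wording on serious adverse reactions could cover severe OHSS, and recording an event does not put the woman in an analysis set.
- *Departures may be balanced.* This is true. A difference by arm is plausible from the open-label design and the injection schedules, but the documents do not show one. The 10% is a dropout allowance, not a forecast of per-protocol exclusions.
- *The definitions already use participants.* Clinical pregnancy, miscarriage, cumulative and OHSS rates are defined as percentages of participants. This helps, but the analysis sentence then decides which participants count.

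A separate analysis plan may exist. It would have to reverse the sentence, not merely add detail to it.

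**Conclusion.** The point holds as a defect in what the protocol states. Intention-to-treat is confined to the MII rate, every other outcome is labelled per-protocol, and the inclusion rule is at odds with that label. On the likelier reading, pregnancy, live birth and severe OHSS are compared in a set selected after randomisation, and women with severe OHSS could be among those removed.

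The size and direction of any bias are unknown. Under the assumptions shown, the false difference in live birth runs from about 1 point or less with near-even exclusions to 10 points at the extreme. The documents do not support quoting one figure from that range as the expected bias, nor saying that OHSS cases will go uncounted. The primary analysis and the sample size are unaffected.

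**What to change.** Replace the second sentence of the analysis-set paragraph so that:

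- clinical pregnancy, miscarriage, live birth and the cumulative rates are analysed in all randomised women as allocated, with the randomised woman as denominator;
- number of oocytes retrieved is analysed as randomised;
- outcomes with oocyte or embryo denominators (fertilisation, top-quality embryo, blastula formation and implantation rates) are analysed by allocated arm in all women who have the denominator, with no exclusion for non-adherence;
- severe OHSS and adverse events are analysed in all women who received any trigger;
- per-protocol is kept as a labelled sensitivity analysis.

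Add to Dropout Criteria and Study Case Discontinuation that outcome collection continues after a woman stops trial treatment. The protocol has a one-year follow-up and follows serious adverse events, but does not say that the outcomes of women who leave are collected.

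The cost is some slight dilution of estimates and the continued follow-up of women who stop. The sample size stays at 90.

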Given that fresh embryo transfer is the preferred option of assisted reproduction, oocyte maturation and ovulation induction by co-administration of GnRH-a and hCG, the dual trigger, have attracted much attention recently. In terms of number of oocytes retrieved, number of MII oocytes, fertilisation rate, top-quality embryos rate, and embryo implantation rate, a meta-analysis found that dual trigger was more advantageous but not statistically different from hCG trigger (4). Dual trigger is available in two ways (5, 6): Concomitant use GnRH-a and low-dose hCG (1000-2500 IU) as trigger drugs 35-37 hours prior to OPU reduces the risk of OHSS in high responders (7). And it can compensate for luteal insufficiency in GnRH-a trigger, which is associated with comparable or even higher pregnancy rates than hCG trigger (6–8)]. Furthermore, combining low-dose hCG with GnRH-a (dual trigger) to induce final oocyte maturation improved the number of oocyte retrieval in poor responders without raising the risk of clinically severe OHSS (9). Another alternative dual trigger approach is co-administration of GnRH-a and hCG for final oocyte maturation, 40 and 34 hours prior to OPU, respectively. Beck-Fruchter R et al. used this trigger to prolong the period between trigger and OPU to successfully obtain mature oocytes and achieve pregnancy, delivery in a patient with empty follicle syndrome (EFS) (10). According to recent findings, normal responders who had a lower rate of mature oocytes (less than 50%) shown a significant increase in the number of oocytes and transferable embryos obtained with this dual trigger method, as well as in the proportion of oocytes obtained to the number of preovulatory follicles, but the pregnancy rates were not conclusive (11, 12). Co-administration of GnRH-a and hCG 40 and 34 hours prior to OPU may therefore be considered novel therapeutic options for patients with poor mature oocyte rates. Additionally, Haas J et al. discovered that decreased conexin43 expression, in combination with enhanced epiregulin and amphiregulin expression, in the GCs of patients undergoing dual trigger may account for the better oocyte and embryo quality (13).

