### Interventions

#### Ovarian Stimulation Protocol

Standard COH protocol with gonadotrophins will be performed using a GnRH-ant protocol. Furthermore, a fixed dosage of GnRH-ant (0.25mg, Cetrorelix; Merck Serono, Darmstadt, Germany) will be used together with 112.5-225 IU/day of recombinant FSH (600IU, Puregon, Merck Sharp & Dohme B.V., Haarlem, Netherlands). Patients will initiate ovarian stimulation treatment with Gn starting on day 3 of the menstrual cycle, the starting dose of Gn will be based primarily on age and BMI, and determined by the patient’s attending physician prior to participation in the study. Subjects will undergo serial transvaginal ultrasound follicle measurements and monitoring of serum oestradiol (E_2_), progesterone (P_4_), and LH levels during the IVF/ICSI cycle to dynamically measured to evaluate the response of ovary, the dose of Gn will be adjusted according to the subject’s response. GnRH-ant (0.25mg/d) will be added on day 5 of ovarian stimulation sustained to the trigger. Trigger when two follicles were ≥ 18mm in diameter or when three follicles were ≥ 17mm in diameter. The following trigger patterns will be used in two groups: (1) hCG-only trigger: injection of recombinant hCG (6500 IU, Ovidrel, European Serono, France) 36 hours before OPU; (2) Dual trigger: co-administration of GnRH-a (Diphereline, 0.1mg, France, Epson) and hCG, 40 and 34 hours prior to OPU, respectively. If a patient has high-risk OHSS (more than 20 follicles over 10 mm in diameter) on the triggering day, a freeze-all strategy will be used. Oocyte retrieval will be performed by transvaginal puncture under transvaginal ultrasound guidance.

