### Randomization and Blinding

On the trigger day, randomization will begin. Individuals will be assigned to one of two groups, A or B, in a 1:1 ratio by computer, using a random sequence of codes in the order of enrolment. The randomization scheme was entered into an online central randomization database (www.medresman.org). A dedicated data specialist will run the online randomization procedure, who will not be involved in patient recruiting or clinical care. The doctors will be notified of the allocation results *via* email after randomization. Allocation concealment will be guaranteed since the service will not divulge the allocation until after the randomization process, i.e. after the baseline visit. Due to the nature of the intervention, we will not blind the patients and doctors on the assigned groups. However, the trial outcome assessors will be blinded to the intervention.

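### Number of oocytes retrieved is compared without adjustment for the follicle count seen before randomisation, which gives up precision at no saving

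*Protocol article*

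**What the plan says.** - **Outcome.** In Reproductive Outcomes, oocyte number heads the secondary list: "The secondary outcomes are number of oocytes retrieved". The other efficacy outcomes there are rates. The Abstract also names oocyte quantity as part of the aim.
- **Test.** Data Statistical Analysis: "The continuous data will be normalized using the two independent samples t-test and presented as mean ± standard deviation". A nonparametric test replaces it if the distribution is not normal. Neither option carries a covariate.
- **Follicle data.** Ovarian Stimulation Protocol: "Subjects will undergo serial transvaginal ultrasound follicle measurements and monitoring of serum oestradiol". In the same section, the decision to trigger depends on follicle diameters, and the freeze-all rule depends on how many follicles exceed 10 mm on the trigger day.
- **Timing.** Randomization and Blinding: "On the trigger day, randomization will begin". Allocation is 1:1 and no stratification factor is mentioned.
- **Rationale.** The Introduction reports that earlier work with this trigger found more oocytes, "as well as in the proportion of oocytes obtained to the number of preovulatory follicles".

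**The concern.** The follicles visible on the last scan are those that will be punctured, so their number is a natural predictor of how many oocytes are retrieved. It is fixed before allocation, and the trigger cannot influence it. A comparison that ignores it leaves the variation between women in follicle number inside the error term.

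What is at stake is the width of the confidence interval for the effect on yield, and the chance of detecting a real effect. The sample size was set for the metaphase-II rate alone, so the oocyte count has no planned power. The statistical analysis plan is not at hand. However, the protocol states which test it will use, so this is a comment on a stated choice and not on a missing detail.

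**Working it through.** **Inputs from the protocol (Sample Size Estimation).** "Suppose that α=0.05 (two-sided) and β=0.10 (90% power"; "the estimated rate of MII oocytes in group B was 40%, and 70% in group A"; "with standard deviations of 40% for each group"; 40 per arm, raised to 45 for 10% dropout.

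**Inputs that are assumptions.** The correlation r between pre-randomisation follicle count and oocytes retrieved (0.3, 0.5, 0.7), and a true difference of 0.5 SD. The SD of the oocyte count is not given, so effects are in SD units.

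**Step 1: the plan's own figure.** n per arm = 2 × (1.960 + 1.282)² × 40² / 30² = 37.4, so 38 by the normal approximation. The t-based calculation gives 39 (power 90.5%), and 40 per arm has 91.2%. Then 40 / 0.90 = 44.4, so 45. The stated 40 and 45 are reproduced to within two women per arm. This calculation concerns the metaphase-II rate only.

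**Step 2: precision of the unadjusted comparison of oocyte number.** SE = √(2/45) = 0.211 SD. The difference detectable with 80% power is (1.960 + 0.842) × 0.211 = 0.59 SD. Power for 0.5 SD is Φ(0.5/0.211 − 1.96) = Φ(0.41) = 66%.

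**Step 3: effect of adjustment.** Linear adjustment for one baseline covariate multiplies the SE by √(1 − r²), apart from the small cost of estimating one slope. The equivalent unadjusted size is 45 / (1 − r²), and power is Φ(0.5 / [√(2/n) × √(1 − r²)] − 1.96). The last column uses n = 40, because outcomes other than the primary are to be analysed per protocol and some women may be excluded.

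| r | SE factor | CI narrower by | Equivalent unadjusted n per arm | Detectable at 80% power, n = 45 | Power, n = 45 | Power, n = 40 |
|---|---|---|---|---|---|---|
| none | 1 | – | 45 | 0.59 SD | 66% | 61% |
| 0.3 | 0.954 | 5% | 49.5 | 0.56 SD | 70% | 65% |
| 0.5 | 0.866 | 13% | 60 | 0.51 SD | 78% | 73% |
| 0.7 | 0.714 | 29% | 88 | 0.42 SD | 91% | 88% |

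**Step 4: chance imbalance.** An imbalance of one standard error in mean follicle count (0.211 SD) moves the unadjusted difference by r × 0.211. That is 0.06, 0.11 and 0.15 SD at r = 0.3, 0.5 and 0.7. These shifts are part of the sampling variation that the 0.211 SD already covers. They are not an additional error.

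**The case against.** The strongest reply is that nothing here is incorrect. An unadjusted two-sample test is valid under randomisation, the outcome is one of about ten secondary outcomes, and the sentence is a general rule in a condensed article that does not forbid adjusted analyses. The gain depends wholly on an assumed correlation. At r = 0.3 it is only about four percentage points of power. Eligibility is narrow (antral follicle count 6 to 15, AMH 1.2 to 3.5 ng/ml) and the trigger rule is common to both arms. Both may restrict the range of follicle number and so weaken the correlation. All of this stands, and it limits the point to efficiency.

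Three stronger readings are tempting, and the document does not support them:
- A reader might infer that a difference in oocyte number could merely reflect more follicles in one arm, so that the test misleads. The standard error of the unadjusted test already allows for such chance imbalance.
- A reader might infer that the analysis contradicts the protocol's own rationale. The Introduction reports the raw increase in oocytes first and the ratio to preovulatory follicles as an addition, so analysing the count is consistent with it.
- A reader might infer that nothing in the design limits imbalance. The article describes a random code sequence in order of enrolment and does not say whether it is blocked, and eligibility itself restricts follicle number.

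Two practical points also stand. The document defines no size at which a follicle counts as preovulatory. The scans are planned, but a recorded count is inferred, chiefly from the over-10 mm rule. Also, Study Population and Recruitment describes allocation after the baseline work-up and before the trial regimen. That is looser than the trigger-day statement on which the covariate's baseline status depends.

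**Conclusion.** The point holds as a modest one. The protocol fixes an unadjusted comparison for oocyte yield although a pre-randomisation follicle measurement exists for every woman. The cost is avoidable imprecision on a secondary outcome for which the trial was not sized. Bias and type I error are not affected.

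The direction follows for any appreciable correlation. The size does not come from the document: the interval would be about 5% to 29% narrower, and power for a 0.5 SD difference would rise by about 4 to 25 percentage points with 45 per arm, over assumed correlations of 0.3 to 0.7. The conclusion relies on randomisation taking place on the trigger day, after the last scan, as Randomization and Blinding states.

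**What to change.** - Prespecify one model for oocytes retrieved, for example ANCOVA on arm, with the follicle count on the last scan before randomisation as covariate.
- State in advance one size threshold for that count. The number over 10 mm is a convenient choice, because the freeze-all rule already needs it on the trigger day. Antral follicle count can be an optional second covariate.
- Report the adjusted difference with its 95% confidence interval, and keep the unadjusted test as supportive.
- Align the wording on timing in Study Population and Recruitment with Randomization and Blinding, so that the covariate is clearly measured before allocation.

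The cost is a sentence or two in the analysis section, one regression, and a check that the count is entered as a data item. No extra visit, scan or participant is needed. Fixing the covariate before the data are seen also removes a later choice that could appear driven by the result.

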### Eligibility Criteria

#### Inclusion Criteria

(1) Expected normal ovarian responder (NOR): 6 ≤ antral follicle counting (AFC) ≤ 15; 1.2 ng/ml ≤ anti müllerian hormone (AMH) ≤ 3.5 ng/ml; basal FSH< 10 mIU/ml; no previous history of cancellation of IVF cycles with low or high ovarian response; (2) Patients with ≥ 50% immature oocytes in the only one previous fresh IVF cycle triggered with hCG; (3) In the previous IVF cycle, standard ovarian stimulation protocol was performed using a GnRH-ant protocol and triggered when two follicles were ≥ 18mm in diameter. 

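### The stated test rule will almost certainly report the primary outcome as medians, not the 30-point mean difference the trial is sized on, and leaves each woman's previous-cycle maturity rate unused

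*Protocol article*

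**What the plan says.** The Reproductive Outcomes section defines the endpoint as a ratio: "The primary outcome is MII oocytes rate (percentage of the number of mature oocytes to the number of oocytes retrieved".

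The Sample Size Estimation section plans on means. It states that "the estimated rate of MII oocytes in group B was 40%, and 70% in group A", "with standard deviations of 40% for each group". It then sets the error rates ("Suppose that α=0.05 (two-sided) and β=0.10 (90% power") and concludes that "the sample size is calculated to be 40 individuals for each group by PASS 15.0", raised to 45 per group for 10% dropout.

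The Data Statistical Analysis section assigns the primary endpoint to the intention-to-treat set but gives it no test or model of its own. Continuous data get a two-sample t-test with mean ± SD. Otherwise: "If the distribution is not normal, use nonparametric tests, which are expressed as the median (interquartile range) [M (IQR". It names no covariate.

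The Inclusion Criteria require at least 50% "immature oocytes in the only one previous fresh IVF cycle triggered with hCG". The maturity rate from an earlier hCG-triggered cycle is therefore on record for every woman before randomization.

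**The concern.** Two features of the stated analysis sit badly with the rest of the protocol.

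- **The effect measure depends on the data.** The planned quantity is a difference in mean per-woman MII rate. Whether the report gives means or medians is decided by the shape of the trial's own data. If the data go to the rank branch, readers get two medians with IQRs. These cannot be set against the 40% and 70% in the sample-size section.
- **A baseline value of the primary outcome is available and unused.** The previous-cycle rate is the same kind of measurement, in the same woman, after an hCG trigger. Adjusting for it can only be expected to help precision, and the data are already in hand.

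At stake are how interpretable the headline result is and some precision. The validity of the test is not in question.

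**Working it through.** **Inputs from the protocol.** Means 40% and 70% (difference 30 points), SD 40 points in each group, two-sided alpha 0.05, power 90%, 40 per group before dropout (Sample Size Estimation).

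**Assumptions not in the protocol.** Beta-distributed rates between women; 6 to 15 oocytes per woman; Shapiro-Wilk at 5% in either arm as the normality check; Mann-Whitney as the nonparametric test; and the correlation between previous-cycle and trial-cycle rates.

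**1. Reproduce the stated size.**
- Two means, z formula: n = 2 × (1.960 + 1.282)² × (40/30)² = 37.4, so 38 per group. The exact t calculation gives 39. Inflating for a rank test by π/3 gives 40 to 41.
- The stated 40 agrees within 2, and 40/0.9 = 44.4, rounded up to 45, matches the dropout step.
- A two-proportions formula gives 56 (63 with continuity correction) and does not match.

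The MII rate is therefore planned as a continuous per-woman value, and the continuous-data rule is the one that applies to it. Unadjusted t-test power at 40 per group is 91.2%.

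**2. What SD 40 implies.** For a variable confined to 0-1 with mean p, the largest possible SD is √(p(1−p)).
- p = 0.40: √0.24 = 0.490
- p = 0.70: √0.21 = 0.458

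An SD of 0.40 is close to both ceilings, so values must pile up near 0% and 100%. A beta distribution with mean m and SD s has a + b = m(1−m)/s² − 1.
- m = 0.40: a + b = 0.24/0.16 − 1 = 0.50, so (a, b) = (0.20, 0.30), median about 24%
- m = 0.70: a + b = 0.21/0.16 − 1 = 0.3125, so (a, b) = (0.22, 0.09), median about 98%

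Both are U-shaped.

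**3. How often the rank branch is chosen** (4,000 simulated trials, 40 per group, beta rates without oocyte counting noise).

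| SD between women | Normality rejected | Mean difference | Average median difference |
|---|---|---|---|
| 40 | 100% | 30 | 69 (95% range 29 to 93) |
| 30 | 100% | 30 | 44 (21 to 64) |
| 25 | 97% | 30 | 38 (21 to 54) |
| 20 | 68% | 30 | 35 (22 to 46) |

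With binomial counts on 6 to 15 oocytes, rejection is again 100% at SD 40 and about 85% at SD 20. At SD 40 the median difference then averages about 70 points, with a 95% range of about 30 to 100.

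**4. Does the switch harm the test?** At SD 40 without counting noise, Mann-Whitney power is 96% against 90% for the t-test. With about 10 oocytes per woman and an underlying SD of 38 it is 93% against 91%. Under no effect, the two-step rule rejects in 5.0% to 5.5% of trials. It does no harm.

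**5. What the previous-cycle rate could add.** With correlation r among the enrolled women, residual variance is multiplied by 1 − r², and 40 women act like 40/(1 − r²).

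| r | Effective n per group | Power |
|---|---|---|
| 0 | 40 | 91.2% |
| 0.15 | 40/0.9775 = 40.9 | 91.8% |
| 0.35 | 40/0.8775 = 45.6 | 94.3% |
| 0.50 | 40/0.75 = 53.3 | 96.9% |

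The entry rule keeps only previous-cycle maturity of 50% or less, which weakens the correlation. In a bivariate normal model that keeps the lowest 10% to 50% of women, a full-range 0.3 falls to about 0.13-0.19 and a full-range 0.5 to about 0.23-0.33. That makes 0.15 to 0.35 the reasonable planning range.

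**The case against.** The best defence is that nothing stated here is invalid. An unadjusted comparison is sound under randomization, the planned size is adequate for it, and the rank test gives up no power. Covariate choice is often left to an analysis plan, which is not shown. All of this stands, and it is why the point is an improvement and not an error. It does not answer the effect-measure problem, because the switch to medians is written into the protocol itself.

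Several stronger readings are tempting, and the protocol does not support them:

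- **That the trial cannot estimate the planned difference.** The t-test branch reports means and would give it. The rank branch is almost certain at SD 40, but at SD 20 it is chosen in about 68% to 86% of simulated trials, depending on whether oocyte counting noise is included. The protocol also names no normality test, so Shapiro-Wilk is an assumption.
- **That a large precision gain is being lost.** No correlation is given, and correlations of 0.3 to 0.5 taken from an unselected population ignore the range restriction from the entry rule.
- **That chance imbalance in strong predictors goes uncorrected after simple randomization.** The protocol does not say whether blocks are used. It does not say that age, AMH, AFC or BMI predict the MII rate, and its eligibility limits narrow all four. Chance imbalance is in any case already reflected in the standard error.

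**Conclusion.** The point holds as a mismatch between the planned and the reported effect, plus an unused baseline. On the protocol's own SD, the primary result would almost certainly be summarised as medians. Their difference averages about 70 points and ranges from about 30 to 100, while the mean difference is 30. This rests on beta-distributed rates and a Shapiro-Wilk check. The U shape itself follows from an SD near its ceiling, and the rank branch remains likely even if the SD is half the planned value.

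The gain from using the previous-cycle rate is probably modest: power of about 92-94% instead of 91%, equivalent to about 41-46 women per group instead of 40. It reaches 97% only if the correlation within the enrolled women is 0.5. The validity, type I error and power of the stated test are not at issue.

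**What to change.** Prespecify one analysis for the primary outcome:

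- **Effect measure:** the difference in mean per-woman MII rate, in percentage points, with a 95% CI.
- **Model:** linear regression of the per-woman rate on arm and previous-cycle MII rate, with robust standard errors. Further covariates such as age and AMH are optional.
- **Normality switch:** remove it for this outcome, and keep the rank test with medians and IQRs as a sensitivity analysis.

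The robust standard errors deal with non-normal, unequal-variance data, so no distribution check is needed to choose the method. The cost is a change of wording before the data are analysed. It needs no extra women, visits or measurements, because the previous-cycle rate has to be known to establish eligibility.
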